## 2.2 Specific objectives

### 2.2.1 Primary objectives

The primary objectives of the trial are as follows:

1. To determine the combined effect of the facility+ community strategies, in controlling blood sugar levels among patients with T2D
2. To determine the effect of the facility+ community strategies, in reducing blood sugar levels among individuals with pre-diabetes
3. To determine the effect of the facility+ community strategies, on retention into care among patients with T2D.
4. To estimate the incremental provider cost per patient of managing patients with T2D, as a result of implementing the facility+ community strategies.
5. To estimate the incremental client cost per patient of managing patients with T2D, as a result of implementing the facility+ community strategies.

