Community mobilization is designed to raise awareness of type 2 diabetes and it’s prevention and management through healthy lifestyle, timely seeking of care and self-management of the disease. It will be used to raise interest in participation in the trial, and it will also help to create and strengthen advocacy for healthy lifestyle in the communities, thereby supporting the goals and activities of the Peer group program, Care Companions / Healthy Lifestyle Buddies and Community Link Team. Key messages for community mobilization will address knowledge gaps identified in the formative research, and they will be compiled in collaboration with relevant stakeholder organizations. Materials for community mobilization will include one-pagers with the key messages and/or visuals. They will be distributed in the Health Facility + Community arm at community screening events, and through partner organizations, Community Link Team, and Peer groups.

*Community Strategy II: Strengthening support from the environment*

This strategy includes strategies for both social and physical environment. ***Peer group program*** will provide an arena for emotional support, practical support and information exchange for individuals living with diabetes and pre-diabetes. Participants in the Health Facility + Community arm are referred to a peer group in their first motivational coaching session. Peer groups meet monthly at a local community venue under the leadership of appointed ***Expert patients*** and co-leaders selected from within each group. A generic ***SMART2D Peer Group Program manual*** (see Appendix) includes topics and activities for 1) building rapport; 2) setting agenda for the group; 3) working with topics selected by the group; 4) receiving and giving ongoing support; and 5) evaluation and adjourning. In addition to the activities, each group meeting will include a brief physical activity break and opportunity for unstructured discussion and sharing. Peer groups are also open for family members and Care Companions / Healthy Lifestyle Buddies. ***Selection criteria*** and recruitment of Expert patients as Peer group program facilitators are outlined in the ***Peer group program manual*** (refer to Appendix). Peer leaders will be asked to give a written commitment for taking the role; in return they will get training, a SMART2D Peer leader certificate, a fixed budget for meeting-related expenses, and a small compensation for each group meeting.

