**Table 3: Details of tools, sources and data collection points for Part III**

| Questionnaires | Source | BL | M2-11 | EL |
| --- | --- | --- | --- | --- |
| **Out of pocket expenditure: Individual and family questionnaire** | Prepared by [name] | X |  | X |
| **Health facility survey – to be administered to head of health facility*** | Prepared by [name] |  | X |  |
| **EPOCH – to be conducted by researcher and collected one per community*** | Environmental Profile of a Community’s Health (Clara Chow – Population Health Research Institute, Hamilton) |  | X |  |

* Not included in this set of data collection tools

| **SECTION 21: Out of Pocket Expenditure related to type 2 diabetes** | | | |
| --- | --- | --- | --- |
| **SECTION 21A: Out of Pocket Expenditure – Outpatient cost** | | | |
| **S.NO:** | **Questions** | **Response** | **Code** |
| A | Do you usually spend any money on medication and other related costs? | 1 Yes regularly  2 Yes occasionally  0 No  **If NO, SKIP to B** | OOPO_1a |
|  | **In the last month, how much did you spend on the following items in relation to treatment of type 2 diabetes?**  *Please record in respective local currency for each setting: Ug Sh (Uganda)/SAR (South Africa)/SEK (Sweden)* | | |
| B | Medicine:  1. Diabetes medication  2. Other medication | 1. └─┴─┴─┴─┴─┴─┴─┘  2. └─┴─┴─┴─┴─┴─┴─┘ | OOPO_1b1  OOPO_1b2 |
| C | Consultation fees  Not applicable = 888 | └─┴─┴─┴─┴─┴─┴─┘  └──┴──┘ | OOPO_1c |
| D | Laboratory tests  Not applicable = 888 | └─┴─┴─┴─┴─┴─┴─┘  └──┴──┘ | OOPO_1d |
| E | Other supplies  Not applicable = 888 | └─┴─┴─┴─┴─┴─┴─┘  └──┴──┘ | OOPO_1e |
| F | Food while at the health facility  Not applicable = 888 | └─┴─┴─┴─┴─┴─┴─┘  └──┴──┘ | OOPO_1f |
| G | Appreciation of health worker  Not applicable = 888 | └─┴─┴─┴─┴─┴─┴─┘  └──┴──┘ | OOPO_1g |
| H | Transport ( to and from facility)  Not applicable = 888 | └──┴──┘ |  |

O

| **SECTION 21B: Out of Pocket Expenditure – Hospitalisation cost** | | | | | |
| --- | --- | --- | --- | --- | --- |
| I | In the past 12 months, how many times were you hospitalized ? | Number of times └─┴**─┘**  **If 0 SKIP to SECTION 21C** | | | OOPI_1i |
| **For each hospitalization** (max 3 – if more, take last 3) can you answer the following questions | | | | | inst_oopi1 |
|  |  | **1** | **2** | **3** |  |

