| V | Ambulance/transport | └─┴─┴─┴─┴─┴─┴─┘  777. I don’t know | └─┴─┴─┴─┴─┴─┴─┘  777. I don’t know | └─┴─┴─┴─┴─┴─┴─┘  777. I don’t know | OOPI_1v1  OOPI_1v2  OOPI_1v3 |
| W | Cost for somebody accompanying me: accommodation | └─┴─┴─┴─┴─┴─┴─┘  777. I don’t know | └─┴─┴─┴─┴─┴─┴─┘  777. I don’t know | └─┴─┴─┴─┴─┴─┴─┘  777. I don’t know | OOPI_1w1  OOPI_1w2  OOPI_1w3 |

| **SECTION 21C: Household Expenditure** | | | |
| --- | --- | --- | --- |
| On average, how much did you spent in your household on the following in the LAST ONE MONTH?” Enter 777 if amount is not known.  *Please record in respective local currency for each setting: Ug Sh (Uganda)/SAR (South Africa)/SEK (Sweden)* | | | |
| A | Food, including such things as rice, meat, fruits, vegetables and cooking oil | └─┴─┴─┴─┴─┴─┴─┘ | HH_1a |
| B | Value of food consumed by the household which is produced/grown in the household | └─┴─┴─┴─┴─┴─┴─┘ | HH_1b |
| C | Gas, electricity, water, telephone and heating fuel | └─┴─┴─┴─┴─┴─┴─┘ | HH_1c |
| D | Transport, repair of vehicles | └─┴─┴─┴─┴─┴─┴─┘ | HH_1d |
| E | Housing rent. If house is not rented, ask about the rental value of patient’s house. | └─┴─┴─┴─┴─┴─┴─┘ | HH_1e |
| F | Education fees and supplies | └─┴─┴─┴─┴─┴─┴─┘ | HH_1f |
| G | Reimbursement of loans | └─┴─┴─┴─┴─┴─┴─┘ | HH_1g |
| H | Insurance premiums or prepaid health plans | └─┴─┴─┴─┴─┴─┴─┘ | HH_1h |
| I | Clothes, shoes and related items | └─┴─┴─┴─┴─┴─┴─┘ | HH_1i |
| J | Goods like washing machines, cooking utensils, stove, radio, furniture, bicycle | └─┴─┴─┴─┴─┴─┴─┘ | HH_1j |
| K | Special occasions including festivals, weddings, funerals, etc | └─┴─┴─┴─┴─┴─┴─┘ | HH_1k |
| L | Others | └─┴─┴─┴─┴─┴─┴─┘ | HH_1l |
| In addition to the above, have you spent any money in the LAST ONE YEAR on any special occasions in your family, illness of other members, purchase of house, car or other assets? 0 = No, 1 = Yes | | | |
| M | Specify |  | HH_1m |
| N | Specify |  | HH_1n |

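### The out-of-pocket questionnaire has no diabetes-attributable item for attending peer groups, so primary objective 5 (incremental client cost) can be understated

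*Protocol*

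**What the plan says.** Protocol section 2.2.1, item 5, states the aim: "To estimate the incremental client cost per patient of managing patients with T2D, as a result of implementing the facility+ community strategies".

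What distinguishes that arm is the community component in section 3.3.3.1: "Peer groups meet monthly at a local community venue". Companions are encouraged to come to the meetings, and going along to peer sessions where feasible is one of the companion's additional tasks in that arm. Table 6 describes monthly visits over a year. Table 8 gives nine sessions at each site.

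The client-cost instrument is Section 21 of the data collection tools (Part III), which only participants with diabetes complete.

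- **Section 21A** asks, for the last month, "how much did you spend on the following items in relation to treatment of type 2 diabetes". Its items are medicines, consultation fees, laboratory tests, "Other supplies", "Food while at the health facility", appreciation of the health worker, and "Transport ( to and from facility".
- **Section 21B** covers hospital stays, including transport. Its companion item is "Cost for somebody accompanying me: accommodation".
- **Section 21C** asks for the household's last-month spending, including food, "Transport, repair of vehicles" and a residual category.

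Table 3 of the data collection tools schedules the questionnaire at baseline and end-line. Protocol Table 15 schedules out-of-pocket expenditure at months 3, 6 and 12.

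**The concern.** An incremental cost is a difference between arms. A cost that only one arm generates belongs in that difference in full. Travel to peer groups, spending at the meetings and a companion's attendance are such costs. The questionnaire ties its diabetes-related travel and food items to the health facility, so these costs have no place of their own.

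A cost cannot be negative. Leaving out one that occurs in a single arm therefore moves the estimate in one direction only: the incremental client cost comes out too low, or unchanged if the omitted cost is zero. The objective is a primary one, and the result would inform whether the strategy is affordable for patients. An analysis plan cannot repair this afterwards, because an expense that was never asked about, or was recorded only inside a household total, cannot be recovered.

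**Working it through.** The plan states no figure for this point, so there is nothing to reproduce. The check has two parts.

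**1. Items set against community-arm activities**

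| Cost arising only in the facility + community arm | 21A | 21B | 21C |
| --- | --- | --- | --- |
| Participant's travel to peer groups | No; travel item is facility only | No; hospital stay only | Inside total household transport |
| Food or other spending at meetings | No; food item is facility only. Some purchases might be put under other supplies | No | Inside household food or the residual category |
| Companion's cost of attending meetings | No | No; accommodation during a hospital stay only | Only if the companion shares the household, and then unattributed |

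No item in 21A or 21B names a community-activity cost. Section 21C cannot substitute: its transport line covers all household travel, whatever the reason. It would also contain the facility fares already reported in 21A, so adding the two would double count.

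**2. Possible size, for travel only**

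Inputs:
- Clinic trips per year for a participant with diabetes: 12 (monthly visits, protocol section 3.8).
- Peer sessions per year, *s*: 9 (Table 8) to 12 (monthly for a year, Table 6).
- Cost of a peer trip relative to a clinic trip, *f*: not given; assumed to lie between 0 (walking distance) and 1 (same fare).
- Full attendance, and the participant's own travel only: assumed.

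Share of diabetes-related travel cost not captured = *s* × *f* / (12 + *s* × *f*).

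| *f* | *s* = 9 | *s* = 12 |
| --- | --- | --- |
| 0 | 0% | 0% |
| 0.25 | 2.25 / 14.25 = 16% | 3 / 15 = 20% |
| 0.5 | 4.5 / 16.5 = 27% | 6 / 18 = 33% |
| 1 | 9 / 21 = 43% | 12 / 24 = 50% |

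In money, if a peer trip costs *c*, the understatement is *s* × *c* per fully attending participant per year, or up to 2 × *s* × *c* if a companion also pays. It is zero if *c* is zero.

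**3. Timing**

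Section 21A asks about the last month. At baseline no peer group has met, so any meeting item would be zero. If nine monthly sessions start early in follow-up, they end around month 9, and last-month recall at month 12 would also give zero. Adding items on the schedule in Table 3 of the tools, with the present recall period, could therefore still miss the whole programme.

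**The case against.** A reader might infer that the questionnaire covers clinic and hospital spending only, that it captures what is common to the arms and omits what is incremental, and that the client-cost estimate is therefore too low by construction, with 43% to 50% missed. The documents do not support that reading, for these reasons.

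- **Section 21C exists.** It records household transport, food and other spending. Peer-group costs are unattributable rather than wholly unrecorded.
- **Part of the increment is captured.** Retention in care is primary objective 3, and in Uganda peer leaders remind members to attend visits. Extra clinic travel, medicines and tests that result would be recorded in 21A.
- **The form shown is the recruitment and baseline set.** The change log says peer-group text was taken out of Section 13. An end-line tool on community activities is still to be finalised, and sites may add questions. A later cost item cannot be excluded.
- **The cost may be small.** Venues are local, and peer leaders receive a budget for meeting expenses. In South Africa community health workers take the companion role. The 43% to 50% is a share of trips, and becomes a share of travel cost only if a peer trip costs as much as a clinic trip.
- **The computation is not described.** Section 3.13.2 sets out a provider-perspective cost analysis only. How client cost is totalled may be left to the analysis plan.

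All of these points stand and limit the claim, but they do not remove it. Table 3 of the tools lists the same questionnaire at end-line, and the variable-naming rule carries items forward by changing the month code. The pending community-activities tool is listed under basic participant data, not expenditure. The leaders' budget is not stated to pay for participants' or companions' travel.

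**Conclusion.** The point holds in a limited form. As written, the questionnaire has no diabetes-attributable item for the costs of attending community meetings, and those costs fall on one arm only. If it is reused at follow-up as scheduled, and client cost is built from Sections 21A and 21B, this component can bias primary objective 5 only towards understating the incremental cost.

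The size is unknown: 0% to 50% of a participant's diabetes-related travel cost under the stated assumptions on trips, attendance and relative fare. Travel is only one part of client cost, so this is not the share of total client cost missed. The form, left unchanged, could not show that the omission is negligible. The direction is firm; the amount is not, and an unseen end-line addition could already close the gap. The change is cheap and worth making.

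**What to change.** In the follow-up versions of Section 21A, for participants with diabetes in all arms (zero where not applicable), add:

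1. number of peer-group or other SMART2D community meetings attended;
2. transport to those meetings, for the participant and for a companion;
3. other spending on those meetings.

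Give these items at the month 3, 6 and 12 visits of Table 15, and reconcile Table 3 of the data collection tools with that schedule. Ask about the period since the previous visit, so that the three rounds together cover the 12 months. Alternatively, ask the usual cost per meeting and multiply by meetings attended, which relies less on memory over the six months before month 12. State that these items enter the client-cost total, and that Section 21C household transport is not added to it.

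The cost is a minute or two more per interview and a somewhat longer recall period than the present one month.

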|  | Study informed consent |  | X |  |  |  |
|  |  |  |  |  |  |  |
| **II. Enrollment & Study ID** | Study ID number assignment |  | X |  |  |  |
|  | Patient registration in Register |  | X |  |  |  |
|  | Patient file creation |  | X |  |  |  |
|  | Patient appointment card |  | X |  |  |  |
|  |  |  |  |  |  |  |
| **III. Physical Measurements** | Height |  | X |  |  |  |
|  | Weight |  | X | X | X | X |
|  | Waist circumference |  | X |  | X | X |
|  | Blood pressure |  | X | X | X | X |
|  | 7-day pedometer steps |  | X |  |  | X |
|  |  |  |  |  |  |  |
| **IV. Biochemical** | FPG (Uganda & South Africa) | X, X | X | X | X | X |
|  | HbA1c (All sites) |  | X |  |  | X |
|  |  |  |  |  |  |  |
| **V. Basic participant data** | Pre-eligibility assessment | X |  |  |  |  |
|  | Eligibility confirmation |  | X |  |  |  |
|  | Eligibility and recruitment check |  | X |  |  |  |
|  | Contact Information |  | X |  |  |  |
|  | Demographic and social measures |  | X |  |  |  |
|  | Medical and medication history |  | X |  |  |  |
|  | Behavioral measures (diet, physical activity, foot care, tobacco use, alcohol consumption) |  | X |  |  | X |
|  |  |  |  |  |  |  |
| **VI. Intervention process measures** | Participant diabetes knowledge |  | X |  |  | X |
|  | Illness perception |  | X |  |  | X |
|  | Social support and sources of support |  | X |  |  | X |
|  | Self-efficacy, autonomy support & self-regulation |  | X |  |  | X |
|  | Psychological adjustment |  | X |  |  | X |
|  | Quality of life & Stress |  | X |  |  | X |
|  | Diabetes treatment satisfaction |  |  |  |  | X |
|  | Out of pocket expenditure |  |  | X | X | X |
|  | Incremental cost to the health facility |  |  | X | X | X |
|  | Adherence to study procedures and to intervention elements |  | X |  |  | X |
|  |  |  |  |  |  |  |
| **VII. Facility forms** | Process evaluation |  |  | X | X | X |
|  |  |  |  |  |  |  |
| **VIII. Community forms** | Environment context measurement (EPOC) |  | X |  |  |  |

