## 3.9 Outcomes of interest:

*Primary outcomes of interest*

Among participants with pre-diabetes, the primary outcome of interest will be reduction in plasma glucose between baseline and month 12 of follow-up. We hypothesize that participants with pre-diabetes in the facility + community arm will on average have a higher reduction in their HbA1c reading by the end of follow-up compared to participants with pre-diabetes in the facility alone arm, and the current practice arm in Uganda.

Regarding participants with type 2 diabetes, research has shown that, reduction of HbA1c level by 1% among such individuals leads to: a) 19% less likelihood of cataracts, b) 16% less likelihood of heart failure, and c) 43% less likelihood of amputations or death due to peripheral vascular disease [Anon 1993]. Further the UK Prospective Diabetes Study (UKPDS) [King et al 1999], and the Diabetes Control and Complications Trial (DCCT) demonstrated that improving HbA1c by 1% for people with type 1 diabetes *or* type 2 diabetes cuts the risk of microvascular complications by 25%. Therefore among participants with diabetes, the primary outcome of interest will also be reduction of their plasma glucoce levels. A participant will be classified as having had their plasma glucose reduced if:

1. Their HbA1c reading at month 12 is reduced to below 53 mmol/mol, or
2. Their HbA1c reading at month 12 is 5 mmol/mol below their baseline reading.

*Secondary outcomes of interest*

Secondary outcomes in this trial will include:

a) Incidence of diabetes among participants with pre-diabetes

b) Incidence of conversion from a state of pre-diabetes to normal plasma glucose levels.

c) Incidence of adverse events, including hospitalizations due to hypo- or hyperglycemia, or complications of diabetes.

d) Behavioral outcomes, including diet, physical activity, foot care, tobacco and alcohol consumption.

e) Costs of implementation of the intervention elements

f) Participant satisfaction with the individual intervention elements, including self-management

g) Differences between the country sites, in regard to baseline context infrastructure for prevention and management of T2D

h) Degree of implementation of intervention elements in each country, and differences between country sites informed by site-specific process evaluations

i) Effect of the interventions on perceptions towards diabetes, life style measures including physical activity, dietary behavior, etc.

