### 3.13.2 Analyses of secondary objectives

1. For the "incidence of progression from pre-diabetes state to diabetes state", we will use Kaplan Meier methods to compare incidence between the two arms. The log-rank test will be used and Kaplan-Meier curves will be plotted for each treatment group.
2. Adverse events, including hospitalizations due to hypo- or hyperglycemia, morbidity. For adverse events outcomes, we must account for the possibility that participants may experience multiple episodes over the study period. Thus, we will use log-binomial models for repeated outcomes to examine the treatment effect on these outcomes
3. For costs outcomes, cost evaluation will be undertaken from the health program provider perspective. The health service use costs of the two strategies will be calculated at 12 months in both arms. Costs incurred between baseline and 12 months will be discounted at ??%. The mean cost of the two groups over 12 months will be compared using non-parametric tests. Results will be reported with 95% confidence intervals and uncertainty will be examined using sensitivity analysis. An incremental cost-effectiveness ratio will be calculated over the 12 months of the intervention. The need or otherwise for cost-effectiveness modeling will depend on there being economically important clinically significant differences in glycaemic control, as determined by the likely impact on and hence, long-term effects on morbidity and mortality. Whether any differences in glycaemic control are important will be informed by reviewing the cost-effectiveness of other interventions that have been evaluated using lifetime models. If such differences do exist, the modeling of the longer-term effects to assess the incremental cost per quality adjusted life-year will be conducted
4. For comparison of differences between the country sites, in regard to baseline context infrastructure situation for prevention and management of diabetes, these are baseline comparisons thus for continuous context variables, we will use the t-test statistic or the equivalent non-parametric test. For categorical context variables we will use the chi-square test statistic.

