**For participants with PRE-DIABETES, END HERE!**

PART III: Selected context measures

Context is multi-layered and highly complex, including micro- and macro-components stretching from individual attitudes and beliefs to the wider socio-political climate. We will attempt to measure only those aspects of context which are relevant to the implementation of SMART2D and thereby the outcome as well. The conceptual figure shown below has been modified from Taplin et al and attempts to describe the most relevant layers for SMART2D and the aspects that will be measured using quantitative data collection tools. Figure 2 shows each aspect that will the measured and the corresponding tools *(in italics)*. The grey circles represent areas not covered by these evaluation tools. Some aspects such as lay support networks have been studied to some extent in the formative part and others such as socio-political climate of each setting will be mainly described using narratives to keep track of temporal changes.

*Figure 2: Context measures and corresponding tools*

*
[figure not shown]
*

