| J | What was the reason for the hospitalization? | 1. Related to diabetes 2. Unrelated to diabetes   777. I don’t know | 1. Related to diabetes 2. Unrelated to diabetes   777. I don’t know | 1. Related to diabetes 2. Unrelated to diabetes   777. I don’t know | OOPI_1j1  OOPI_1j2  OOPI_1j3 |
| K | How many days were you hospitalised ? | **└──┘** | **└──┘** | **└──┘** | OOPI_1k1  OOPI_1k2  OOPI_1k3 |
| L | What was the total cost of your stay in the hospital? | └─┴─┴─┴─┴─┴─┴─┘ | └─┴─┴─┴─┴─┴─┴─┘ | └─┴─┴─┴─┴─┴─┴─┘ | OOPI_1l1  OOPI_1l2  OOPI_1l3 |
|  | Can you divide the costs for each hospitalisation into the following categories?  *Please record in respective local currency for each setting: Ug Sh (Uganda)/SAR (South Africa)/SEK (Sweden)* | | | | inst_oopi2 |
| M | Cost for medication while in the hospital | └─┴─┴─┴─┴─┴─┴─┘  777. I don’t know | └─┴─┴─┴─┴─┴─┴─┘  777. I don’t know | └─┴─┴─┴─┴─┴─┴─┘  777. I don’t know | OOPI_1m1 OOPI_1m2 OOPI_1m3 |
| N | Payment for accommodation | └─┴─┴─┴─┴─┴─┴─┘  777. I don’t know | └─┴─┴─┴─┴─┴─┴─┘  777. I don’t know | └─┴─┴─┴─┴─┴─┴─┘  777. I don’t know | OOPI_1n1  OOPI_1n2  OOPI_1n3 |
| O | Emergency room fees | └─┴─┴─┴─┴─┴─┴─┘  777. I don’t know | └─┴─┴─┴─┴─┴─┴─┘  777. I don’t know | └─┴─┴─┴─┴─┴─┴─┘  777. I don’t know | OOPI_1o1  OOPI_1o2  OOPI_1o3 |
| P | Consultation (doctor) fees | └─┴─┴─┴─┴─┴─┴─┘  777. I don’t know | └─┴─┴─┴─┴─┴─┴─┘  777. I don’t know | └─┴─┴─┴─┴─┴─┴─┘  777. I don’t know | OOPI_1p1  OOPI_1p2  OOPI_1p3 |
| Q | Surgery | └─┴─┴─┴─┴─┴─┴─┘  777. I don’t know | └─┴─┴─┴─┴─┴─┴─┘  777. I don’t know | └─┴─┴─┴─┴─┴─┴─┘  777. I don’t know | OOPI_1q1  OOPI_1q2  OOPI_1q3 |
| R | Supplies (bandages, syringes, catheters, etc) | └─┴─┴─┴─┴─┴─┴─┘  777. I don’t know | └─┴─┴─┴─┴─┴─┴─┘  777. I don’t know | └─┴─┴─┴─┴─┴─┴─┘  777. I don’t know | OOPI_1r1  OOPI_1r2  OOPI_1r3 |
| S | Laboratory test | └─┴─┴─┴─┴─┴─┴─┘  777. I don’t know | └─┴─┴─┴─┴─┴─┴─┘  777. I don’t know | └─┴─┴─┴─┴─┴─┴─┘  777. I don’t know | OOPI_1s1  OOPI_1s2  OOPI_1s3 |
| T | X-rays, scans etc | └─┴─┴─┴─┴─┴─┴─┘  777. I don’t know | └─┴─┴─┴─┴─┴─┴─┘  777. I don’t know | └─┴─┴─┴─┴─┴─┴─┘  777. I don’t know | OOPI_1t1  OOPI_1t2  OOPI_1t3 |
| U | My own food | └─┴─┴─┴─┴─┴─┴─┘  777. I don’t know | └─┴─┴─┴─┴─┴─┴─┘  777. I don’t know | └─┴─┴─┴─┴─┴─┴─┘  777. I don’t know | OOPI_1u1  OOPI_1u2  OOPI_1u3 |

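### No instrument shown captures the adverse-event outcome as defined, and the schedules disagree on when the only hospitalisation questions are asked

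*Protocol*

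**What the plan says.** Protocol section 3.9 lists as secondary outcome c: "Incidence of adverse events, including hospitalizations due to hypo- or hyperglycemia, or complications of diabetes". Outcomes a and b are limited to participants with pre-diabetes; c has no such limit. Section 3.13.2, item 2, says that "we must account for the possibility that participants may experience multiple episodes over the study period", and then that "we will use log-binomial models for repeated outcomes to examine the treatment effect on these outcomes".

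The schedule (section 3.8, Table 15) has no row for adverse events or hospitalisations. Its row "Medical and medication history" is marked at baseline only. Out-of-pocket expenditure is marked at M3, M6 and M12.

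In the data collection tools, hospitalisation appears only in Part III, Section 21B, which belongs to the out-of-pocket cost module. Item I asks "In the past 12 months, how many times were you hospitalized". Details are then taken for each admission, limited to "max 3 – if more, take last 3". Item J codes the reason as "1. Related to diabetes 2. Unrelated to diabetes", or don't know. Part II closes with the instruction "For participants with PRE-DIABETES, END HERE", so participants with pre-diabetes never reach Part III. Tools Table 3 places the cost module at baseline and end-line, with nothing between.

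**The concern.** Outcome c is the only outcome in the plan that names adverse events. What can be said about it depends on who is asked, what is coded and over which period. The protocol and its tools fix all three, and no analysis plan can recover data that were not collected.

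If the tools are used as printed, about half of the planned participants are asked nothing about admissions. In the other half, the hypo- and hyperglycaemic admissions that the outcome names cannot be told apart from other diabetes-related ones, and no episode can be placed in time. A difference between arms in such events, in either direction, might then go unseen or be mis-timed.

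**Working it through.** No stated figure has to be reproduced. The check traces the outcome to the schedule and the tools.

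**1. Who is asked.** Planned numbers per arm come from the notes to Figure 15.

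| Site | Arms | Pre-diabetes per arm | Pre-diabetes total | All per arm | All total |
|---|---|---|---|---|---|
| Uganda | 3 | 124 | 372 | 265 | 795 |
| South Africa | 2 | 142 | 284 | 292 | 584 |
| Sweden | 2 | 174 | 348 | 353 | 706 |
| Sum | | | 1,004 | | 2,085 |

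1,004 / 2,085 = 48%. The figure prints an overall N of 1997, which is not the sum of its own site totals; against 1997 the share is 50%. Either way this is a share of people, not of events.

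**2. What is coded.** Item J has three answers: related to diabetes, unrelated, don't know. No item asks the admission date. The count in item I has no cap, but the reason belongs to the per-admission details, so it is lost for any admission before the last three.

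**3. Over which period.** Follow-up is 12 months. A 12-month recall asked at month *t* reaches 12 − *t* months before enrolment.

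- Table 15 timing, wording unchanged:
  - M3: 12 − 3 = 9 months before enrolment (75% of the window).
  - M6: 12 − 6 = 6 months (50%).
  - M12: 0 months.
  - Months 0–3 of follow-up fall in three windows, months 3–6 in two and months 6–12 in one. Without dates, duplicate reports cannot be removed.
- Tools Table 3 timing:
  - The baseline window lies wholly before enrolment.
  - The end-line window covers months 0–12 exactly once.
  - Participants who die or are lost before M12 report nothing. Section 3.10 projects up to 10% loss to follow-up.

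The two schedules cannot both be followed, and each has a different weakness.

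**4. Complications.** Kidney disease, foot ulcers and loss of vision (MED_1d to MED_1f) sit in the medical history section of the tools. Table 15 and tools Table 1 both place it at baseline only. Section 3.8 lists a medical history assessment and a clinical evaluation among the follow-up assessments. That text contradicts the schedule, and neither entry names an adverse-event item or form.

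**The case against.** The strongest reply is that nothing in the protocol makes Section 21B the source of outcome c. It is a cost module for type 2 diabetes and serves the primary objective on client cost, so leaving out participants with pre-diabetes suits its purpose. The instructions to site teams describe the printed set as the instruments for screening, recruitment and baseline, where 12-month recall is normal. Section 3.8 plans clinical evaluation at follow-up, participants with diabetes attend monthly, and patient files are kept. Outcome c can also be read as a composite of diabetes-related admissions, which the existing code would record.

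Much of this stands. A reader might infer that the outcome cannot be computed at all. The documents do not support that, because clinic files or follow-up forms could hold events. A reader might also infer a fixed bias towards no difference. With a constant event rate and the three Table 15 reports added together, 0.25 + 0.5 + 1.0 = 1.75 person-years of recall are on study and 0.75 + 0.5 + 0 = 1.25 are before enrolment. A true rate ratio of 0.50 would then appear as (1.25 + 1.75 × 0.50) / 3.0 = 0.71, and 0.70 as 0.83. That needs Table 15 timing, unchanged wording and summed overlapping reports. Nothing in the plan says the reports will be summed, and the M12 report alone covers follow-up once. These ratios illustrate a risk and are not part of the finding.

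The reply does not supply a source. The same instructions also call the set the complete survey tools, and tools left out are flagged as such (community activities, facility survey, EPOCH); no adverse-event form is among them. Part IV is not shown, but it is announced as process and fidelity checks. Even on the composite reading, participants with pre-diabetes are not asked and admissions carry no date.

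**Conclusion.** The point holds in this form: no instrument shown captures outcome c as defined, no other source is named, and the schedules conflict.

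- On the tools as printed, 1,004 of 2,085 planned participants (48% by headcount) are asked nothing about hospitalisation. The share of events missed is unknown, because the documents give no adverse-event rate for pre-diabetes.
- In participants with diabetes, admissions are undated and hypo- and hyperglycaemia are not coded. The observation period depends on which table is followed. The recall that reaches 9 and 6 months before enrolment arises only under Table 15 with unchanged wording.
- Complication items are baseline-only in two tables, against the text of section 3.8.

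This rests on the tools as shown. If follow-up forms or clinic files are the intended source, the defect narrows to their not being named and to the unreconciled schedules. It should be corrected, but it does not show that the outcome is beyond recovery.

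**What to change.** 1. State in section 3.9 or 3.8 where outcome c comes from, including clinic files if they are meant.
2. Move the hospitalisation count and reason (items I and J) ahead of the pre-diabetes stop, so that all participants answer them.
3. At follow-up visits ask about admissions 'since your last study visit' and record the admission date. Keep 12-month recall at baseline only.
4. Code the reason as hypoglycaemia, hyperglycaemia, other diabetes complication, unrelated or unknown. Apply the limit of three admissions to the cost details only.
5. Repeat MED_1d to MED_1f at M12.
6. Make section 3.8, Table 15 and tools Tables 1 and 3 agree.

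This re-words existing questions at visits already planned, with no new visit or test. The cost is a few extra interview minutes, mainly for participants with pre-diabetes.
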